#### b. Economic evaluation

The aim of the economic evaluation is to assess the cost-effectiveness of collaborative care for the treatment of depressive disorders in the general hospital setting. A cost-utility analysis (CUA) will be applied, the results of which will be expressed as cost per QALY. The economic evaluation will be undertaken from a societal perspective, so all relevant effects and costs due to resource utilisation within the health care system (direct medical costs) and costs due to production losses (productivity costs) will be included.

Since the collaborative care intervention used in this study is new intervention, a unit price per session is not known yet. To determine a reference price, a detailed cost-price study will be performed. Therefore, we will perform measurements of time for face-to-face contacts as well as indirect time per contact (e.g. consultations of other specialists) for a total of 20 sessions. Furthermore, we will estimate overhead costs based on the information of the financial department of the hospital. This will result in an estimate of the actual costs per contact. The unit cost estimate per contact will be used as a reference price per contact for the collaborative care intervention.

The TiC-P will be used to assess the costs [87]. The TiC-P iscommonly applied in economic evaluations of treatments in mental health care. For instance, the TiC-P was recently used in a large naturalistic trial on the cost-utility of brief psychological treatment for depression and anxiety [88].

Calculating the total direct medical costs, the total number of medical contacts (outpatient visits, length of stay in hospital, use of medication, etc.) will be multiplied by unit costs of the corresponding health care services. Reference unit prices of health care services will be applied, and adjusted to the year of the study according to the consumer price index [106].

The second section of the TiC-P includes a short form of the Health and Labour questionnaire (HLQ) for collecting data on productivity losses [107]. The Short-Form HLQ (SF-HLQ) consists of three modules that measure productivity losses: absence from work, reduced efficiency at work and difficulties with job performance [108]. The number of days absent from work and the actual cost of hours missed at work due to health-related problems are valued according to the average value added per worker by age and gender per day and per hour, respectively. If respondents indicate that they have been absent for the entire recall period, data will be collected from the time when the period of long-term absence started. This additional information will be used to value the production losses according to the friction cost method [109,110]. The friction cost method takes into account the economic circumstances that limit the losses of productivity to society, which are related to the fact that a formerly unemployed person may replace a person who becomes disabled [109].

For the economic evaluation, the effects will be measured according to utility scores. In addition to the clinical outcome parameters, the utility scores will supply additional information about the impact of collaborative care on the treatment of MDD compared to the impact of CAU on the general health related quality of life. Furthermore, the results can be compared to a broad range of other health care interventions, also outside the field of mental health care.

The cost-utility will be evaluated by relating the difference in direct medical costs per patient receiving collaborative care or CAU to the difference in terms of QALYs gained, which yields a cost per QALY estimate. Furthermore, we will also estimate the cost per QALY, including the productivity costs.

In the case of missing data on costs and/or effects, and the additional uncertainty this introduces, we will use 'multiple imputation' [111]. We will use the Monte Carlo Markov Chain (MCMC) approach to impute the missing values. The uncertainty will be assessed with bootstrapping, and the results will be presented in acceptability curves [112].

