### Embedding in the general hospital care setting

The collaborative care framework used in this study will last for a maximum of 22 weeks, and comprises the following four elements: a) contracting, b) antidepressant medication, c) PST, and d) manual-guided self-help. These treatments are superimposed on the basic model of patient and provider adherence-enhancing techniques.

The diabetes, cardiology, and pulmonary outpatient clinics of the OLVG will participate in this study. The elements of the collaborative care framework are divided among different disciplines in order to maximize effect of the interventions. The elements provided by each discipline performing the elements are shown in Table 1:

**Table 1 T1:** Embedding in the hospital setting

Task	Discipline
Screening	Department nurse/Researcher
Contractor	Psychiatrist/Consultative psychiatric nurses
Care manager	Consultative psychiatric nurses
Prescription of antidepressants	Psychiatrist
Problem Solving Treatment	Consultative psychiatric nurses

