### Treatment of patients in the intervention group

In the *collaborative care framework *used in this study, active collaboration of the patient with the treatment is enhanced. The care is tailored to the patient's needs within an active team, which consists of the patient, the care manager and the consulting psychiatrist. If the care manager experiences difficulties in this process, (s)he can consult the psychiatrist. Within the team the need for and assessment of the required treatment will be determined, and a treatment plan will be formulated. Subsequently, the care managers will co-ordinate the care and evaluate each step, together with the patient. According to the stepped care principle, treatment response will be monitored once every two weeks [54]. If necessary, each treatment step will be followed by a subsequent step to improve the outcome. For patients who solely receive PST, this subsequent step can involve six extra sessions of PST and/or adding antidepressant medication (AD), or switching to antidepressant medication only. The same method will be applied to patients who are treated with both PST and antidepressant medication.

The framework also includes *patient and provider adherence-improving techniques*. Provider adherence-improving interventions are administered by the research group. Provider adherence has been enhanced in an earlier study in primary care, in which psychiatrists instructed general practitioners by means of consultations, combined with phone calls and written instructions that were distributed regularly [55]. Such an approach was also found to be feasible and effective in the USA [56]. In the present study, the adherence of care managers will be improved in a similar way. Patient adherence will be improved by contracting and psycho-education [55,57].

In the present setting, the collaborative care framework includes four treatment options superimposed on adherence-enhancing techniques. The patients will have the choice of receiving antidepressant medication, but PST, contracting and manual-guided self-help are obligatory.

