### Power calculations

In this study, the PHQ-9 will be used as the primary outcome measure. In order to detect a standardised difference of 0.5 standard deviation in the primary outcome measure (which can be considered as a clinically relevant difference), 2 × 63 patients are needed when two-sided testing and 80% power is assumed. Intention-to-treat analysis will be applied. Therefore, 126 patients will be needed. An improvement of more than five points on the PHQ-9 can be considered a clinically relevant difference [86].

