## Discussion

There is a high prevalence of chronically ill patients suffering from depression, and interventions for the treatment of comorbid depression are urgently needed. Evidence for effective treatment does exist, but these are frequently not applied. The current trial is designed to implement evidence-based treatments for depression in the general hospital setting, and to test the hypothesis that these treatments are more effective and cost-effective than CAU. This is a pragmatic trial; hence, the objective of the trial is to assess the benefits of the treatment in routine clinical practice. The relationship between depressive symptoms and the course of several chronic illnesses suggests that this line of research may be of considerable importance in the field of public health.

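### The price per collaborative care contact leaves no place for the research group's provider support, a cost that falls on the intervention arm only

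*Protocol article*

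**What the plan says.** The section on treatment in the intervention group states that the framework contains techniques to improve the adherence of both patients and providers. On the provider side it says: "Provider adherence-improving interventions are administered by the research group". It cites an earlier primary care study in which psychiatrists supported general practitioners through consultations, telephone calls and regular written instructions, and says that care managers here will be supported in a similar way. The embedding section likewise describes the four treatments as resting on these techniques.

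The sections on recruitment of departments and on training add that members of the research group train the staff, and that the research team closely monitors the care managers. Patients in usual care have no care manager.

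The economic evaluation derives a reference price per contact from "measurements of time for face-to-face contacts as well as indirect time per contact (e.g. consultations of other specialists) for a total of 20 sessions", together with overhead figures from the hospital's financial department. Direct medical costs are numbers of contacts and other care multiplied by unit prices. The cost per QALY relates the difference between arms in cost per patient to the difference in QALYs. The same section declares a societal perspective: "so all relevant effects and costs due to resource utilisation within the health care system (direct medical costs", with productivity costs included as well.

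**The concern.** The intervention that is tested and the intervention that is priced differ. The tested one includes support of the care managers by the research group. The priced one consists of patient contacts with their direct and indirect time, plus hospital overhead. The support is neither a patient contact nor, as described, something the hospital's finance department would report as overhead. Patients cannot report it on the cost questionnaire either.

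The support exists in one arm only, so leaving it out biases the cost difference in a known direction, in favour of collaborative care. The QALY difference still contains whatever the support achieved. The ratio would then credit an effect without its cost. Cost-effectiveness is the trial's secondary outcome, and the protocol intends to compare the result with a broad range of other health care interventions, so the price should cover what was delivered.

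**Working it through.** **The plan's own figure.** The protocol gives no cost, QALY gain or cost per QALY to reproduce. Its one reproducible number is the sample size: "2 × 63 patients are needed when two-sided testing and 80% power is assumed", for a difference of 0.5 SD. With alpha 0.05 (not stated, assumed), n = 2 × (1.960 + 0.842)² / 0.5² = 62.8, so 63 per arm and 126 in total. It reproduces. It matters here only because about 63 patients would share any one-off cost.

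**Does the support cost cancel?** Let C1 and C0 be the mean costs per patient under the stated rule, S a cost that both arms bear before randomisation, h the support hours per intervention patient and w the cost per hour.

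- Screening: (C1 + S) − (C0 + S) = C1 − C0. It cancels exactly.
- Provider support: (C1 + h·w) − C0 = (C1 − C0) + h·w. It does not cancel. If omitted, the cost difference is too low by h·w, and the cost per QALY by h·w / ΔQ when the QALY gain ΔQ is positive.

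**Is there a place for h·w in the stated price?** Taking the components in turn:

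- Direct contact time covers the time of the nurse or psychiatrist with the patient.
- Indirect time per contact may cover a care manager's own time in a support call. It hardly covers the time of the person giving the support.
- Overhead is taken from the hospital's accounts, and the support is not described as a hospital cost.

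**Illustrative size.** Every euro and QALY input below is an assumption. With h = 2 hours and w = EUR 50 to 100, h·w = EUR 100 to 200 per patient.

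| Support per patient | ΔQ = 0.05 | ΔQ = 0.02 |
|---|---|---|
| EUR 100 | 100 / 0.05 = EUR 2,000 per QALY | 100 / 0.02 = EUR 5,000 per QALY |
| EUR 200 | 200 / 0.05 = EUR 4,000 per QALY | 200 / 0.02 = EUR 10,000 per QALY |

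Over a wider assumed range, EUR 0 to 300 per patient and 0.02 to 0.10 QALY, the addition runs from nil to 300 / 0.02 = EUR 15,000 per QALY. As an example of the shift, an assumed incremental cost of EUR 1,000 and gain of 0.05 QALY give EUR 20,000 per QALY. With support added this becomes 1,100 / 0.05 = EUR 22,000 to 1,200 / 0.05 = EUR 24,000.

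**Training.** This is a one-off cost. Each EUR 1,000 spread over 63 patients is 1,000 / 63 = EUR 15.87 per patient, or 15.87 / 0.05 = about EUR 317 per QALY. The amount falls as more patients are treated, which is why it suits a sensitivity analysis better than the base price.

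**The case against.** The strongest reply is that omission is an inference. The protocol promises a detailed cost-price study, its indirect time is introduced by an open-ended example, and no line excludes support or training. A condensed article may leave item-level costing to a fuller plan. In addition, the close monitoring of care managers is meant to ensure correct delivery, which reads partly as trial fidelity work that an adopting hospital would not pay for.

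Part of this stands. The care managers' own time in support calls may be captured, and monitoring done only for the trial should not be charged. But the article does not merely stay silent: it states how the price is built, and the supporters' time has no place in that rule. Labelling the support as part of the framework also rules out treating all of it as research activity.

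A reader might go further and infer that leaving out screening also understates the cost per QALY. Table 1 lists screening first and is introduced with "The elements of the collaborative care framework are divided among different disciplines in order to maximize effect of the interventions", and the Discussion says that "the objective of the trial is to assess the benefits of the treatment in routine clinical practice". The documents do not support that inference:

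- The same section's explicit list has four elements: contracting, antidepressants, problem solving treatment and self-help. Screening is not among them.
- The stated aim of the economic evaluation concerns treatment of depressive disorders, and only patients positive on both the PHQ-9 and the MINI are randomised. For that question a cost common to both arms rightly cancels.
- Against unscreened care the QALY difference would change too, because controls are identified, told that they can consult their general practitioner, and monitored. In the EUR 20,000 example, take an assumed EUR 5 per screen and the low end of the protocol's depression prevalence, 13%, as the yield. Screening then adds 5 / 0.13 = EUR 38 per patient. The ratio is 1,038.46 / 0.05 = EUR 20,769 if screening alone brings no benefit. If screening alone gave controls 25% of the gain, it is 1,038.46 / 0.0625 = EUR 16,615. The direction is not fixed.
- Charging case-finding to collaborative care while keeping QALYs from screened controls would mix two comparators, and the trial has no unscreened arm to resolve this.

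**Conclusion.** The point holds for provider support. The protocol makes it part of the intervention, it serves one arm, and the stated price per contact plus hospital overhead does not cover the research group's time. This contradicts the claim that all relevant health care costs are included. The bias in cost has a known direction and equals the support cost per patient. Its size cannot be determined from the document: EUR 2,000 to 10,000 per QALY rests entirely on the assumed hours, hourly cost and QALY gain, and the true figure could be small. The conclusion also assumes that at least some of the support is a running part of the model and not purely trial conduct. It does not extend to screening.

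**What to change.** In the economic evaluation section, state that the research group's hours of adherence support for care managers will be logged, that purely research or trial-fidelity work will be recorded separately and left out, and that the remaining hours will be priced and added to the intervention's reference price. Add staff training cost, spread over the patients treated, in a sensitivity analysis. Word the cost-effectiveness conclusion as applying to patients already identified by screening. No ratio that charges case-finding to collaborative care alone is needed.

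The cost is a small logging effort by the research group and a rule for sorting support from research activity. The downside is a slightly less favourable cost per QALY. The design, sample size and patient burden do not change.

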### Time-frame of the study

The preparatory period will be 6 months. After approval has been received from the Medical Ethical Committee, the care managers are trained. The inclusion and intervention phase will take 22 months. The follow-up phases will be 3 (T_1_), 6 (T_2_), 9 (T_3_), and 12 months (T_4_) after inclusion. Data-analyses will take another 6 months, with interim reporting every year. The entire study period will last for 4 years.

### Ethical principles

The study has been planned, and will be carried out in accordance with the principles laid down in the Helsinki declaration (Edinburgh, Scotland amendment, October 2000).

Participation in the study is voluntarily. The patients will be informed in writing and verbally about the global features of the study, the possible benefits of participating in the experimental group, and the societal aspects of the study. The patients will be explicitly informed of the fact that they can withdraw their consent to participate at any time, without specification of any reasons, and with no negative consequences for their future treatment. Patients who wish to withdraw from the study will receive CAU.

Informed consent will be obtained twice from the patients. First, prior to completion of the baseline questionnaire, and again before inclusion in the study.

The names of the patients and other confidential information will be treated according to the medical confidentiality rules and patient data will be separated from patient names. The patients will be anonymous, because each participant will be identified in the database by a number and a code. The codes will only be available for the participating investigators.

Furthermore, all study-related data will be stored on a protected Trimbos Institute server, access to which granted exclusively to the members of the research team. The investigators will be responsible for the administration of the study. The results of the surveys will not be disclosed to the hospital staff.

The Medical Ethical Committee of the OLVG has approved of the study protocol (study no WO06-066).

## Discussion

There is a high prevalence of chronically ill patients suffering from depression, and interventions for the treatment of comorbid depression are urgently needed. Evidence for effective treatment does exist, but these are frequently not applied. The current trial is designed to implement evidence-based treatments for depression in the general hospital setting, and to test the hypothesis that these treatments are more effective and cost-effective than CAU. This is a pragmatic trial; hence, the objective of the trial is to assess the benefits of the treatment in routine clinical practice. The relationship between depressive symptoms and the course of several chronic illnesses suggests that this line of research may be of considerable importance in the field of public health.
